### Outcome measures

#### Primary outcome measures

Feasibility (acceptability of study design, recruitment strategy, random allocation and data collection procedures).

Feasibility will be evaluated using mixed methods to explore intervention delivery, participants’ acceptability, challenges and issues faced during the study and recommended changes to the study design. Moreover, the number of protocol deviation; an estimate of the cost of carrying out the study; time required for recruitment, data collection, and analysis will be evaluated.2)Recruitment rate

The total number of participants recruited into the study, number of participants recruited per month, number of invited women, and number of excluded participants before and after the dental screening and reasons for exclusion.3)Adherence

Percentage of sachet consumed during the study per group (based on the number of returned sachet by pregnant women in their monthly visit); average number of follow-up visits, percentage of participants who provide full data at baseline throughout pregnancy and up to 6–8 weeks postpartum.4)Attrition rate

Number of dropouts in each study arm and reasons for dropout.

#### Secondary outcome measures

Changes in mean and SD of percentage of sites with bleeding on probing (BOP) and CAL between postpartum and baselineChanges in maternal blood levels of biomarkers of inflammation (CRP, IL-6 and MMP-9)Changes in maternal blood levels of 25(OH) D, glucose, insulin, calcium, parathyroid hormone and lipids (HDL, LDL and triglycerides)Neonatal blood levels of 25(OH) D and calcium

### Sample size

This is a feasibility study, and thus the final sample size will be determined by the number of participants that are feasible to recruit within the timescale and budget of the project. For feasibility studies, a minimum of 12 subjects per group is proposed by Julious [54], and a total sample size of 70 subjects is proposed by Teare et al. [55] for a continuous outcome. Since we are planning a 2 × 2 factorial RCT, a sample size of 120 (30 per group), would be enough to detect a realistic event and allowing for 58% dropout rates (considering a sample size of 70), with sufficient precision and minimal bias for the estimates, as well as the existence of an additive interaction between the two interventions.

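### The sample size section gives 58% as the tolerable dropout, but 58% is the share that must be retained to keep 70 of 120 women; the tolerable dropout is about 42%

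*Protocol article*

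**What the plan says.** The Sample size section of the protocol article first says that the final number will be whatever can be recruited within the project's time and budget. It then cites two rules for feasibility studies. For the first, "a minimum of 12 subjects per group is proposed by" one source; for the second, "a total sample size of 70 subjects is proposed by" another, for a continuous outcome. The trial has four arms ("Since we are planning a 2 × 2 factorial RCT"), and the section settles on "a sample size of 120 (30 per group"). It says this number is adequate, "allowing for 58% dropout rates (considering a sample size of 70"), with sufficient precision and little bias for the estimates.

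No other section states a dropout rate or gives another basis for the 58%. Under Primary outcome measures, attrition is defined as "Number of dropouts in each study arm and reasons for dropout". That text contains no percentage and no error; it matters here only because it makes attrition a primary outcome.

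**The concern.** The bracket in the sentence ties the dropout allowance to a target of 70. Losing 58% of 120 women does not leave 70, so the sentence gives the sample size a robustness that it does not have, and the error is in the trial's favour.

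What is at stake is limited but real. The same sentence rests its claim of sufficient precision on this allowance. Estimating effect sizes and variability for a definitive trial is the first secondary objective in Table 1, so the number of women left to supply those estimates matters. Estimating attrition is also among the primary objectives, and a reader of the results may well set the observed dropout beside the planned allowance.

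**Working it through.** **Inputs, all from the Sample size section**
- Planned total: N = 120, as 4 arms of 30.
- Target to which the allowance is tied: n = 70.
- Stated dropout allowance: 58%.
- Other cited rule: 12 per group, so 4 × 12 = 48 in total.

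**1. Where 58% comes from**

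Share retained = n/N = 70/120 = 0.583, or 58.3%. This matches the printed figure to rounding, but it is the share that stays.

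**2. Tolerable dropout on the stated basis**

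d = 1 − n/N = 1 − 70/120 = 50/120 = 0.417, or 41.7%.

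Check: 70/(1 − 50/120) = 120. The overstatement is 58.3 − 41.7 = 16.7 percentage points (unrounded: 20/120).

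**3. What 58% dropout would leave**

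- Total: 120 × (1 − 0.58) = 50.4, about 50 women.
- Per arm: 30 × 0.42 = 12.6, so 12 to 13.
- Shortfall against 70: about 20.
- Total against the 12-per-group rule: 50 against 48, so the rule is met with about 2 women to spare, provided that losses are spread almost evenly over the arms.

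Keeping 70 at 58% dropout would need 70/0.42 = 166.7, so 167 women randomised.

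**4. Other readings that might give 58%**

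| Reading | Calculation | Result |
|---|---|---|
| Target inflated by 58% of itself | 70 × 1.58 | 111, not 120 |
| Excess over target, relative to target | (120 − 70)/70 | 71%, not 58% |
| Base of 12 per group | 1 − 48/120 | 60%, not 58% |
| Base of 12 per group, inflated for 58% dropout | 48/0.42 | 115 (rounded up), not 120 |
| Final sample of 50 | 50/0.42 | 120 (rounded up), but the document never names 50 |

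Only the retained share, 70/120, gives 58% from figures that the document names.

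**5. Effect on precision (illustration)**

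For a normally distributed outcome with one SD pooled over four arms, the relative standard error of the SD is about 1/√(2 × df), with df = women − 4.
- 70 women: 1/√(2 × 66) = 8.7%.
- 50 women: 1/√(2 × 46) = 10.4%.

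The ratio is about 1.20, so the SD would be estimated about 20% less precisely with 50 women than with 70.

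**The case against.** The strongest case on the other side is that nothing in the trial depends on this number. The 120 was not obtained by inflating 70 for dropout; the section says that feasibility of recruitment within time and budget decides the size. Recruitment closed in May 2018. Correcting the percentage alters no sample size, randomisation, analysis or participant protection. About 50 completers would also still satisfy the only figure that the section calls a minimum, 12 per group. All of this stands. It limits the consequence, but it does not make the sentence true, because the sentence ties its allowance to 70 and not to 48.

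A reader might infer more than the document supports, in four ways:
- **That 70 is a required minimum.** The text uses that word only for 12 per group; 70 is a total proposed by a cited source.
- **That attrition between 42% and 58% would wrongly be passed as acceptable.** No section judges attrition against 58% or any other threshold. The outcome is descriptive, the objective is to estimate the rate, and the 12-per-group rule in the same section implies a different bound (60%).
- **That the wrong rate will be carried into the definitive trial.** The 58% is a planning allowance, and Table 1 makes estimating attrition an objective in its own right. Nothing says that the allowance will be reused.
- **That the trial is too small.** The slip shows that the allowance is misstated, not that 120 is inadequate.

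**Conclusion.** The stated allowance is wrong as written. On its own basis, a total of 70 out of 120, the design tolerates about 42% dropout and not 58%. The claim of sufficient precision at 58% dropout is therefore unsupported by the figure it cites, although the 12-per-group rule would still be met on average.

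The conclusion needs no assumption beyond the section's own numbers and the ordinary meaning of dropout. That the retained share was printed in place of the dropout share is an inference, though a close one, since no other figure named in the section reproduces 58%. The finding does not depend on it: whatever the cause, 58% dropout from 120 does not leave 70. The precision comparison in the working also assumes a normal outcome and a common SD across arms, and serves only as illustration.

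This is an arithmetic error in one clause, and its effect is confined to how the sample size is justified.

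**What to change.** Restate the clause so that percentage and target agree. Either of these would do:
- allowing for up to about 42% dropout (50 of 120), leaving 70 women (17 to 18 per arm); or
- if a 58% allowance was really intended, say that about 50 women (12 to 13 per arm) would remain, remove the reference to 70, and rest the justification on the 12-per-group rule.

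The cost is one sentence. Under the first option the stated tolerance becomes less favourable; under the second, the precision claim has to be made for about 50 women. Neither needs further enrolment, a change to the definition of the attrition outcome, or a new attrition ceiling.

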### Objectives

The primary and secondary objectives are described in Table 1.

**Table 1 Tab1:** Objectives of the IMPROVE feasibility trial

Primary	Secondary
1. Feasibility of recruitment strategy for local health service and participants	1. Estimates of effect size and variability to enable accurate sample size and power calculations for a definitive RCT
2. Time necessary to recruit participants	2. Identification of any differences across age groups and other socio-demographic factors with regards to attrition rate
3. Acceptability of the study design and random allocation	3. Identification of key barriers and enablers to adoption, and large-scale implementation, of the IMPROVE trial are
4. What the most appropriate inclusion/exclusion criteria are	4. Definition of required for economic analysis and if they can be collected reliably
5. Estimates of compliance, satisfaction, follow- up and attrition rates	5. The capacity of the research team to embed this study into routine practice in the Public Health Centres
	6. To determine the initial effects of the intervention, time and intervention-time interaction on inflammatory biomarkers concentrations and periodontitis status

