## Methods/design

### Study design and setting

The IMPROVE trial is a 2 × 2 factorial feasibility RCT with a parallel process evaluation, i.e. the groups are not cross-over [35], conducted among pregnant women with an existing diagnosis of periodontitis. During recruitment, participants are allocated to one of four intervention arms using a permutated block randomisation matrix (Fig. 1). The arms are as follows:Semi-skimmed powdered milk fortified with additional sachet of 500 mg calcium and 500 IU vitamin D and early PT (PT during pregnancy)Semi-skimmed powdered milk fortified with additional sachet of 500 mg calcium and 500 IU vitamin D and late onset PT (PT after delivery)Semi-skimmed powdered milk with placebo sachet and early PTSemi-skimmed powdered milk with placebo sachet and late onset PT

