### Statistical analysis

Baseline characteristics of participants will be summarised using descriptive statistics (i.e. means and standard deviations for normally distributed continuous variables, medians and ranges for skewed continuous variables, frequencies and proportions for categorical/binary variables), for all four intervention arms and total sample. All analyses will be according to the intention-to-treat approach, including all participants, regardless of adherence to the study protocol. To determine the effects of the intervention, time and group-time interaction on outcomes (inflammatory biomarker concentrations and periodontitis status), one-way repeated measures ANOVA will be used. Intervention will be regarded as a between-subject factor and time with three-time points (T0, T1 and T2) as a within-subject factor. Mean change of biomarker concentrations, number of sites with bleeding on probing and clinical attachment level (periodontal status) will be compared between the four treatment groups using ANCOVA, adjusted for their baseline values. A *P* value < 0.05 will be considered statiscally significant.

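### The Sample size section says 120 women suffice for an additive interaction, but gives no interaction size, SD or power, and the design can detect only large interactions

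*Protocol article*

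**What the plan says.** The design is stated under Study design and setting: "The IMPROVE trial is a 2 × 2 factorial feasibility RCT with a parallel process evaluation". The two factors are the sachet (fortified or placebo) and the timing of periodontal therapy (during pregnancy or after delivery).

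The Sample size section first says that the final size depends on how many women can be recruited within time and budget. It then cites two rules for feasibility studies, a minimum of 12 per group and a total of 70 for a continuous outcome. From these it concludes that "a sample size of 120 (30 per group), would be enough to detect a realistic event", while "allowing for 58% dropout rates (considering a sample size of 70"), with adequate precision and little bias, "as well as the existence of an additive interaction between the two interventions". No effect size, SD or power accompanies the statement.

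Under Statistical analysis, mean changes "will be compared between the four treatment groups using ANCOVA, adjusted for their baseline values", and a P "value < 0.05 will be considered statiscally significant". Table 1 lists as a secondary objective: "Estimates of effect size and variability to enable accurate sample size and power calculations for a definitive RCT".

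**The concern.** A statement that a sample size is enough for an interaction needs an interaction size, an SD and a power. None is given. The two cited rules, as the section describes them, are minimum sizes for a feasibility study and do not concern an interaction contrast. The protocol also treats effect size and variability as things this trial is meant to estimate, so the inputs for such a statement were not in hand.

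In a balanced 2 × 2 trial, the interaction (the difference of differences) has twice the standard error of a main effect. A size that is tolerable for main effects can therefore be far too small for the interaction.

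The results are meant to inform a definitive trial. Whether each component can be analysed there at the margins of the factorial depends on whether the components interact. A reader who has been told that 120 is enough could take a non-significant interaction as evidence that there is none.

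**Working it through.** **Reproducing the plan's figure.** No interaction calculation can be reproduced, because no size, SD or power is stated. The only derivation that can be checked is the step between 120 and 70. The ratio 70/120 = 58.3% is the share retained; the matching dropout is 1 − 70/120 = 41.7%. Taken literally, 58% dropout with 70 remaining would need 70/(1 − 0.58) = 167 women, not 120. The two sizes the section itself uses, 120 and 70, are therefore carried forward.

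**Inputs from the protocol.** Four equal arms; 30 per arm with 120 analysed, on average 17.5 per arm with 70; significance level 0.05; ANCOVA adjusted for baseline.

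**Assumptions.** Two-sided test, 80% power, equal SD in the arms, and baseline correlation ρ of 0.5 to 0.8. The protocol states none of these. Results are in SDs of the analysed outcome, meaning the residual SD when ANCOVA is used.

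**Standard errors.**
- Interaction: SE = SD × √(4/n per arm). This gives √(4/30) = 0.365 SD with 120 and √(4/17.5) = 0.478 SD with 70.
- Main effect at the margins: SE = SD × √(4/N). This gives √(4/120) = 0.183 SD and √(4/70) = 0.239 SD, half the interaction SE.

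**Detectable interaction.** The normal approximation is (1.960 + 0.842) × SE, which gives 1.02 SD with 120 and 1.34 SD with 70. The noncentral t with N − 4 degrees of freedom gives 1.03 and 1.36 SD. For comparison, the detectable main effect with 120 is 2.802 × 0.183 = 0.51 SD.

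**Baseline adjustment.** In raw outcome SDs, multiply by √(1 − ρ²), which is 0.866, 0.714 and 0.600 for ρ = 0.5, 0.7 and 0.8.

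| | 120 analysed | 70 analysed |
|---|---|---|
| Detectable interaction, SD of analysed outcome | 1.03 | 1.36 |
| In raw SD, ρ = 0.5 | 0.89 | 1.18 |
| In raw SD, ρ = 0.7 | 0.74 | 0.97 |
| In raw SD, ρ = 0.8 | 0.62 | 0.82 |
| Power for 0.5 SD, unadjusted | 27% | 18% |
| Power for 0.5 raw SD, ρ = 0.5 | 35% | 22% |
| 95% CI half-width, main effect | 0.36 | 0.48 |
| 95% CI half-width, interaction | 0.72 | 0.95 |

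The half-widths are t(0.975; N − 4) × SE: 1.98 × 0.365 = 0.72 and 2.00 × 0.478 = 0.95 for the interaction; 1.98 × 0.183 = 0.36 and 2.00 × 0.239 = 0.48 for a main effect.

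**Size that a 0.5 SD interaction would need.** n per arm = 4 × (1.960 + 0.842)²/0.5² = 126 (rounded up), or 504 in total, at 80% power, unadjusted and before dropout.

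**The case against.** The sentence is loosely built. The interaction phrase could depend on the verb of detection, on the allowance for dropout, or on the precision of the estimates. Study design and setting favours an estimation purpose: it speaks of approximate effects that will feed a later, adequately powered trial. This is fair, and the sentence should not be treated as an unambiguous power statement. On any of these readings, however, it says that 120 is adequate with respect to the interaction and gives nothing in support. A half-width of 0.72 SD is not sufficient precision to separate a 0.5 SD interaction from zero.

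A reader might infer that nothing below 1 SD can ever be detected. The protocol does not support that. It plans baseline-adjusted ANCOVA, which lowers the threshold in raw SDs, and the 1 SD figure also rests on an assumed power and a two-sided test.

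A reader might infer that the plan will judge the component interaction at P < 0.05. It does not say so. The only interaction named under Statistical analysis is group by time, the ANCOVA compares four groups, and the significance rule is general. Misreading a non-significant result is a risk, not a planned step.

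A reader might take 58% as the true dropout and work with about 50 women. The section ties that percentage to 70 remaining, so it is the retained share, and figures for 50 would rest on a slip.

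Finally, the primary outcomes are feasibility measures and no primary conclusion depends on the interaction. That stands, and it limits the consequence.

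**Conclusion.** The concern holds in a limited form. The Sample size section credits 120 women, with 70 remaining, with adequacy for an additive interaction that the protocol does not support. Under the stated assumptions (80% power, two-sided 5%, full difference of differences), only interactions of about 1.03 SD (120) or 1.36 SD (70) of the analysed outcome are detectable. With baseline correlations of 0.5 to 0.8 these become about 0.89 to 0.62 and 1.18 to 0.82 raw SD. Even at a correlation of 0.8, 70 completers give only about 40% power for 0.5 raw SD. If the interaction is coded as half the difference of differences, the 120-woman threshold reads about 0.51 SD, but it is the same contrast.

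This does not show that the feasibility sample is too small, since a feasibility trial need not be powered for an interaction. It shows an unsupported adequacy statement, which matters for what the trial can say about interaction when the definitive trial is planned. It should be corrected; it does not threaten the primary feasibility conclusions.

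**What to change.** In Sample size, delete the statement that the size is enough to detect a realistic event and an interaction. State instead the expected 95% CI half-widths in SDs of the analysed outcome: about 0.36 (120) or 0.48 (70) for each main effect, and 0.72 or 0.95 for the interaction. Add that they are smaller in raw SDs after baseline adjustment. In the same sentence, correct the dropout figure to 41.7%, because 58% is the share retained.

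In Statistical analysis or at reporting, add one conditional sentence: if the sachet-by-periodontal-therapy interaction is reported, it is given as an estimate with its 95% CI, and a non-significant result is not used as evidence of no interaction in planning the definitive trial.

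The cost is two sentences and a less favourable claim. It needs no extra participants and no design change, and although recruitment has ended it can still be done at reporting.

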### Patient and public involvement

Initially, we held meetings with directors and health professionals at the centre to get details on the prenatal care routine and logistics, socioeconomic and demographic profile of service users, numbers of pregnant women attending per month, and whether the centre offered free dental treatment and nutritional counselling for pregnant women. Subsequently, managers and health professionals at the centre were consulted on how to implement the project with minimal interference in their routine practice. Also, informal consultations with female heath care users (*n* = 4) and pregnant women (*n* = 15) attending the centre were performed to know their opinion about the study, if they considered it interesting for the population, if they had any suggestions on how the project could be implemented, how researchers could invite pregnant women to participate, how the pregnant women would adhere to the proposed protocol, if they would consume the milk and if they had any suggestion on how the team could help in the maintenance of the consumption until the end of the gestation. The views and suggestion of health care professionals and service users were taken into consideration during the implementation of the project.

### Statistical analysis

Baseline characteristics of participants will be summarised using descriptive statistics (i.e. means and standard deviations for normally distributed continuous variables, medians and ranges for skewed continuous variables, frequencies and proportions for categorical/binary variables), for all four intervention arms and total sample. All analyses will be according to the intention-to-treat approach, including all participants, regardless of adherence to the study protocol. To determine the effects of the intervention, time and group-time interaction on outcomes (inflammatory biomarker concentrations and periodontitis status), one-way repeated measures ANOVA will be used. Intervention will be regarded as a between-subject factor and time with three-time points (T0, T1 and T2) as a within-subject factor. Mean change of biomarker concentrations, number of sites with bleeding on probing and clinical attachment level (periodontal status) will be compared between the four treatment groups using ANCOVA, adjusted for their baseline values. A *P* value < 0.05 will be considered statiscally significant.

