### Randomisation, allocation concealment and blinding

To avoid information bias, regarding influence of interviewer by knowledge of group allocation of participants, randomisation took place after baseline assessment. An online randomisation system with a random mixture of permuted block sizes, stratifying participants by current smoking habit (yes vs. no) was provided and concealed by *Sealed Envelope Ltdtm*.

Due to the nature of the intervention (early vs. late PT), complete blinding of the intervention was not possible. However, dentists and participants were blinded to group allocation regarding milk fortification. Outcome assessment is blinded, and the dentist performing the final periodontal examination is not aware of group allocation regarding both placebo or fortified sachet and PT before or after delivery.

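### The planned repeated-measures ANOVA conventionally keeps only women with every visit, against the all-participants promise, and its intervention main effect is diluted by the pre-randomisation visit

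*Protocol article*

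**What the plan says.** Under Statistical analysis, the protocol article sets the analysis population: "All analyses will be according to the intention-to-treat approach, including all participants, regardless of adherence to the study protocol". The first model serves this aim: "To determine the effects of the intervention, time and group-time interaction on outcomes", meaning biomarker concentrations and periodontitis status. For it, "one-way repeated measures ANOVA will be used", and "Intervention will be regarded as a between-subject factor and time with three-time points (T0, T1 and T2) as a within-subject factor". A second analysis takes mean changes, "compared between the four treatment groups using ANCOVA, adjusted for their baseline values".

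Three other places bear on this:

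- Randomisation, allocation concealment and blinding: "randomisation took place after baseline assessment".
- Sample size: 120 women, 30 per group, "allowing for 58% dropout rates (considering a sample size of 70" women).
- Timing of periodontal measures: the Abstract (Methods) lists periodontal measurements among data collected at all three time points. Dental examination places the full periodontal examination at T0 and T2 only.

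**The concern.** There are two separate difficulties.

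**Who is analysed.** Conventional repeated-measures ANOVA needs a value at every level of the within-subject factor. A woman seen at T0 and T1 but lost before T2 is dropped entirely, and her T1 value is lost with her. ANCOVA of change cannot use a woman without the follow-up value. The stated population and the stated method therefore part company as soon as visits are missed, and the Sample size section allows for heavy loss. If loss relates to a woman's earlier values or characteristics, the completers are a selected group. The article treats this as an open question, since secondary objective 2 in Table 1 is to look for differences in attrition by age and socio-demographic factors.

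**What the main effect estimates.** T0 is measured before allocation, so the expected difference between arms there is zero. With T0 as one of three response levels, the between-subject effect of intervention averages that zero with the two post-baseline differences. Anyone reading it as the size of the effect would read it too small.

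**Working it through.** **Inputs from the article.** 120 randomised, 30 per group; response visits T0, T1 and T2; randomisation after baseline; a target of 70 women and a stated 58% dropout; significance level 0.05.

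**Assumptions, not in the article.** Effect d = 0.5 SD at T1 and T2; equal between-visit correlation r of 0.3 to 0.7; a two-group contrast; a two-sided test.

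**1. The plan's dropout figure.** 120 × (1 − 0.58) = 50.4 women, not 70. Keeping 70 of 120 is 70/120 = 58.3% retention, or 41.7% dropout. The 58% looks like retention written as dropout. That is a separate slip. I use 41.7% as the tolerated loss, and nothing below depends on the 58%.

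**2. Women kept by a complete-case analysis**, 120 × (1 − dropout):

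| Dropout | Women analysed | Per arm |
|---|---|---|
| 10% | 108 | 27.0 |
| 20% | 96 | 24.0 |
| 30% | 84 | 21.0 |
| 41.7% | 70 | 17.5 |

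If instead visits are missed independently, with 20% missing at each follow-up (assumed), 120 × 0.8² = 77 women are complete, while 120 × (1 − 0.2²) = 115 have at least one follow-up value.

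**3. Dilution of the main effect.** The main effect is the mean over visits of the difference between arms.

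- Three visits, effect d at T1 and T2: (0 + d + d)/3 = 0.667d.
- Three visits, any effects d1 and d2: (0 + d1 + d2)/3 is two thirds of (d1 + d2)/2, so the loss against the mean post-baseline effect is one third whatever the pattern.
- Two visits, T0 and T2 only: (0 + d)/2 = 0.5d.

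A simulation of 2,000 trials (60 v 60, d = 0.5 SD, r = 0.5, T2 missing completely at random in 30%) kept 84 women on average. The mean estimates among completers were 0.33 SD for the main effect, 0.50 SD for post-baseline mean minus T0 (the group-time contrast), and 0.50 SD for baseline-adjusted ANCOVA of the post-baseline mean.

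**4. Power with 70 completers** (35 v 35, d = 0.5 SD, r = 0.5, t test). Variances are in units of the single-visit variance:

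| Estimate | Effect | Variance | Power |
|---|---|---|---|
| Main effect including T0 | 0.667d | (1+2r)/3 = 0.667 | 39% |
| Group-time contrast, post-baseline mean minus T0 | d | (1+r)/2 + 1 − 2r = 0.75 | 66% |
| Baseline-adjusted ANCOVA at T2 | d | 1 − r² = 0.75 | 66% |
| Baseline-adjusted mean of T1 and T2 | d | (1+r)/2 − r² = 0.50 | 83% |

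The efficiency of the main effect relative to the last row is (4/9)/[(1+2r)/3] × [(1+r)/2 − r²], which gives 0.47, 0.33 and 0.20 at r = 0.3, 0.5 and 0.7. The fairer comparison with what the article already plans is 39% against 66%.

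**The case against.** Several points on the other side are sound.

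- **The plan already holds undiluted analyses.** The group-time interaction and the baseline-adjusted ANCOVA are in the same paragraph, and the maternal secondary outcomes are defined as changes, which those two address. This stands: the dilution concerns one term only.
- **A reader might infer that the trial's intervention effect as a whole is shrunk, or that the diluted estimate will size the definitive trial.** The article supports neither. Secondary objective 1 asks for effect size and variability without saying that they come from the main effect.
- **A reader might infer that an all-participants analysis is impossible under this plan.** That is too strong. The sentence qualifies inclusion by adherence and does not claim complete outcome data. An analysis plan that is not shown could add imputation, and some long-format ANOVA routines keep incomplete subjects. What stands is that the method as named, in its conventional form, does not deliver the population as stated.
- **The 83% is not a fair benchmark for a per-visit reading.** It belongs to a pooled T1/T2 mean. On complete data, a mixed model read at T2 alone has the same 66% as the ANCOVA already planned. Its gain lies in the partial data.
- **A mixed model with T1 and T2 as responses and baseline as covariate would still omit women with no follow-up value.** Correct, so the fix keeps T0 as a constrained response.
- **Taking 50 completers as the expected loss would overstate the problem.** The Sample size section gives a tolerance, and its own target is 70.
- **The primary outcomes are feasibility, recruitment, adherence and attrition.** These models serve secondary objectives, which lowers the severity.

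**Conclusion.** The point holds in a limited form and is of moderate severity. First, the all-participants statement and conventional repeated-measures ANOVA do not fit together once visits are missed: 96, 84 or 70 of 120 women would be analysed at 20%, 30% or 41.7% dropout, and the ANCOVA of change has the same weakness for women without the follow-up value. This assumes the usual complete-case form of the method and no imputation rule elsewhere.

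Second, the between-subject intervention main effect is two thirds of the mean post-baseline effect for outcomes measured three times. That follows from randomisation after T0 and needs no assumed effect size. The power figures do rest on assumed d and r and are illustrative only. The group-time interaction and the baseline-adjusted ANCOVA are unaffected.

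For periodontal outcomes the size depends on an unresolved conflict between the Abstract, Dental examination and Statistical analysis. If only T0 and T2 are measured, the three-visit model cannot be fitted, and a two-visit main effect would be one half of the T2 effect.

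**What to change.** 1. Replace the repeated-measures ANOVA with a restricted-maximum-likelihood mixed model: T0, T1 and T2 as responses, a common T0 mean across arms, treatment-by-visit terms and an unstructured covariance. Every woman with any measurement then enters the model under missing at random. A woman with only T0 informs the baseline mean and variance but adds no direct information on the treatment difference.
2. Read the treatment effect at T1 and at T2. Do not interpret the main effect that includes T0, and do not carry it forward into sample-size work for a definitive trial.
3. Reconcile the Abstract, Dental examination and Statistical analysis on whether periodontal measures are taken at T1. If only T0 and T2 are, fit the same constrained model with two visits, or use the planned baseline-adjusted ANCOVA at T2 and state that it excludes women without a T2 value.

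The cost is a few sentences of statistical text and some extra programming, with no change to data collection. The price in assumptions is missing at random, which should be stated.
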